#### Laboratory measurements

Twelve-hour fasting blood samples will be collected from all participants at baseline and at the end of the study to analyze lipid profile (total cholesterol, high-density lipoprotein [HDL] cholesterol, and triglycerides) and glycated hemoglobin (A1c), as well as to perform a 75-g OGTT in which glucose will be measured at 0 and 120 minutes. For the lipid profile, venous blood samples (5 ml) will be collected in separator gel serum tubes (Vacuette®; Greiner Bio-One, Monroe, NC, USA). Total cholesterol and triglycerides will be determined with an enzymatic colorimetric method (Cobas c702; Roche Diagnostics, Indianapolis, IN, USA). HDL cholesterol will be determined with a homogeneous enzymatic colorimetric assay (Cobas c702). For A1c, a venous blood sample (4 ml) will be collected in ethylenediaminetetraacetic acid (EDTA)-treated tubes (Vacuette®), and levels will be determined with an high-performance liquid chromatography method (VARIANT II TURBO HbA1c kit; Bio-Rad Laboratories, Hercules, CA, USA) certified by the National Glycohemoglobin Standardization Program, which is aligned with that of the International Federation of Clinical Chemistry. The clinical pathology department of the Hospital de Clínicas de Porto Alegre participates in the A1c External Quality Assurance Program, in which it has demonstrated adequate performance [46]. For plasma glucose from OGTT, venous blood samples (4 ml) will be collected in Vacuette® tubes with sodium fluoride, and results will be determined with an enzymatic ultraviolet (UV)-hexokinase method (Cobas c702).

On a different day from the OGTT, an LMTT will be conducted at baseline and at the end of the study to assess not only glucose and insulin response to a meal but also changes in C-peptide, to estimate insulin sensitivity and β-cell function, and to evaluate changes in hormones such as PYY, GLP-1, PP, and ghrelin, which are involved in satiety and hunger regulation [47]. To assess this eight-point glucose-insulin curve (− 30, − 15, 0, 30, 60, 120, 180, and 240 minutes), blood samples will be collected into Vacuette® tubes with sodium fluoride for glucose (4 ml) and with separator gel serum tubes for insulin (5 ml). Serum and plasma will be obtained after centrifugation (3500 rpm, 15 minutes, room temperature) and kept on ice until analysis. The measurements will be taken at the Hospital de Clínicas de Porto Alegre Clinical Pathology Unit. Glucose will be determined using an enzymatic UV-hexokinase method (Cobas c702), whereas insulin will be determined using a chemiluminescence microparticle immunoassay (ARCHITECT Ci4100; Abbott Diagnostics, Lake Forest, IL, USA).

For further hormonal analysis, two venous blood samples (4 ml) will be collected in EDTA-treated tubes (Vacuette®) during the LMTT. In one of the tubes, 40 μl of dipeptidyl peptidase 4 inhibitor (K579; Tocris/Bio-Techne, Minneapolis, MN, USA) will be immediately added to prevent degradation; plasma will be obtained by centrifugation at 1500 rpm and 4 °C for 10 minutes, with the aliquots stored at − 80 °C. The other plasma sample will be centrifuged at 3500 rpm and room temperature for 15 minutes, aliquoted, and stored at − 80 °C for further analysis. PYY_3–36_ is planned to be measured using a commercially available enzyme-linked immunosorbent assay kit (catalogue no. EKE-059-02; Phoenix Pharmaceuticals, Burlingame, CA, USA) according to the manufacturer’s instructions. Fasting and postprandial plasma ghrelin, active GLP-1, C-peptide, and PP concentrations are planned to be measured in the same assay using the human gut hormone panel LINCOplex kit (EMD Millipore, Burlington, MA, USA). This multiplex assay kit uses antibody-immobilized beads to simultaneously quantify these peptide hormones. These analyses are planned to be done in the end of the study when the last individual completes the protocol.

For GA, fasting venous blood samples (5 ml) will be collected during the LMTT in separator gel serum tubes (Vacuette®). Serum will be obtained after centrifugation (3500 rpm, 15 minutes, room temperature) and stored at − 80 °C for subsequent determination. GA measurement will involve the GlycoGap enzymatic method (Diazyme Laboratories, Poway, CA, USA), which measures the amount of glycated serum protein (mmol/L) but not GA specifically. However, due to similar reaction principles, GA levels can be calculated from the total albumin concentration. This method had more analytical precision, with intra- and interassay coefficients of variation of 3.5% and 8.7%, respectively, in previous analyses performed in our laboratory [48].

#### Assessment of insulin sensitivity and β-cell function

Insulin sensitivity and β-cell function will be estimated using static and dynamic measures based on glucose, C-peptide, and insulin measurements taken during the LMTT. The homeostatic model assessment (HOMA) insulin resistance (HOMA-IR) index can be calculated in two ways: estimating IR, in which HOMA-IR = fasting plasma insulin (FPI; μUI/ml) × fasting plasma glucose (FPG; mmol/L)/22.5, and estimating β-cell function, in which HOMA-β = (20 × FPI)/(FPG − 3.5) [49]. The calculator used for this purpose is available online [50].

The LMTT provides a means of assessing insulin secretion patterns in more physiological conditions because these tests include the incretin effect, which follows oral nutrient ingestion. Insulin sensitivity and β-cell responsivity to glucose will be determined as previously described [51]. Plasma glucose and insulin concentrations will be used to determine LMTT indices of insulin sensitivity (Matsuda insulin sensitivity index [MISI]). Pancreatic β-cell function will be determined by calculating the LMTT disposition index.

#### Intervention procedures

At the end of the baseline evaluation, each participant will be prescribed a hypocaloric diet aimed at reducing his or her initial weight by at least 3% in 4 weeks. While on the diet, the participants will receive five weekly visits for tDCS intervention, either active or sham according to prior randomization. A registered dietitian blinded to the tDCS intervention will visit each participant weekly to confirm diet adherence and to make any necessary adjustments to the diet. Participants will be strongly instructed not to change their current physical activity during the trial. Body weight will also be assessed weekly with the same bioelectrical impedance scale used in the baseline evaluation (3-hour fast, light clothes, barefoot).

If a participant withdraws or is removed from the study for any reason, all research-related activities for that individual will be immediately discontinued. Final clinical, anthropometric, and laboratory examinations will be collected from willing participants. Intention-to-treat and per-protocol analyses will be performed.

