**Methods/design:**

Overweight or obese adults between 20 and 50 years of age with stable weight over the last 4 months will be selected for a 4-week randomized clinical trial of fixed-dose tDCS (20 sessions; 5 consecutive weekdays/wk, 2 mA, 20 minutes) over the right dorsolateral prefrontal cortex associated with a weight loss diet. The subjects will be randomly assigned in a 1:1 ratio and stratified by sex to active tDCS + diet or sham tDCS + diet. The study will be conducted at the Endocrine and Metabolism Unit of the Hospital de Clínicas de Porto Alegre, Brazil. The primary outcome is weight loss. Energy and macronutrient consumption, as well as adherence to the diet, will be assessed using 3-day weighed dietary records. Changes in blood glucose and plasma insulin will be assessed, and participants will complete self-report questionnaires to assess changes in mood and food behavior. All analyses will be done on a per-protocol and intention-to-treat basis.

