### Outcomes

The primary outcomes will be reductions in body weight and BMI from baseline and reduction or maintenance of the prescribed energy and macronutrient intake during the 4-week intervention. The secondary outcomes will be reduced hunger, desire to eat, and food craving scores compared with baseline; reductions in fasting and postprandial responses of plasma glucose, insulin, GA, hunger hormones such as ghrelin; and an increase in the blood levels of hormones that participate in the regulation of satiety, such as PYY_3–36,_ GLP-1, and PP [47]. These hormones will be measured to understand mechanisms behind a possible effect of tDCS in weight, desire to eat, food cravings, or glycemic control and variability.

The exploratory outcomes will include the number of participants achieving a 3% reduction or more in body weight compared with baseline; improvements in insulin sensitivity and β-cell function compared with baseline; changes in body composition, such as reduced waist and hip circumferences and reduced body fat mass, compared with baseline; changes in glycemic variability, such as reduced MAGE compared with baseline; changes in depression and anxiety scores compared with baseline; and acute changes in subjective feelings of desire to eat, mood, and attention between pre- and post-tDCS sessions.

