### Statistical procedures

#### Sample size

The sample size was calculated on the basis of a significant reduction in the amount of calories ingested after a single 20-minute session of active tDCS (*F*_1,8_ = 8.4, *p* = 0.02, ηp^2^ = 0.5) [12]. Three types of analysis were performed using G*Power 3.1.9.2® software, considering a power of 80% and an α of 0.05, as follows: effect size (*f*) = 1.0, 10 subjects; effect size (*f*) = 0.8, 12 subjects; and effect size (*f*) = 0.6, 20 subjects. In another study, a 14.2% reduction in the amount of calories ingested was observed after 8 consecutive days of active tDCS sessions. The authors considered a medium effect size (*d*) > 1.09 as sufficient for their findings [13]. Following these assumptions, a total of at least ten subjects would be required in each group to detect a medium-sized effect. Because of possible dropouts, we will include an additional 40% of participants in this study.

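### Week-4, 3-month and 6-month weights are not secured for randomised participants who leave but would still attend, although intention-to-treat is promised

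*Protocol article*

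**What the plan says.** The Intervention procedures section of the protocol article deals with departures in three consecutive sentences. The first is the rule. For anyone who withdraws or is taken out of the trial, whatever the cause, "all research-related activities for that individual will be immediately discontinued". The second keeps something back: "Final clinical, anthropometric, and laboratory examinations will be collected from willing participants." The third names the analysis sets: "Intention-to-treat and per-protocol analyses will be performed." The abstract (Methods/design) repeats the commitment more broadly: "All analyses will be done on a per-protocol and intention-to-treat basis."

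The Outcomes section sets what has to be measured: "The primary outcomes will be reductions in body weight and BMI from baseline", over the 4-week intervention, alongside dietary intake. The Design overview adds a reassessment of weight at 3 and 6 months. While a participant is on treatment, "Body weight will also be assessed weekly with the same bioelectrical impedance scale used in the baseline evaluation", after a 3-hour fast. On account of dropouts, the Sample size section says "we will include an additional 40% of participants in this study".

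**The concern.** An intention-to-treat comparison of weight change at 4 weeks needs, as far as possible, a week-4 weight from everyone randomised, including those who did not finish the intervention. The rule on departures works against this. It covers removal by the study team as well as withdrawal by the participant. It also ends research activity in both cases without asking whether the person would still come for a weighing.

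The sentence on final examinations softens the rule but gives no time point. Staff could read it as an examination on the day of exit or as attendance at the ordinary end-of-treatment assessment. For someone who leaves in week 1 or 2, these are different measurements, because the diet is meant to produce its loss over four weeks.

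This is a rule about collecting data, so it is not something that an analysis plan can repair later. An analysis plan can say how missing weights are handled, but it cannot supply weights that staff were told not to obtain. People may well leave a weight-loss programme for reasons linked to how their weight is going. If so, the missing values fall where they do most harm to the comparison.

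**Working it through.** **1. The text on departures, side by side (Intervention procedures).**

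| Question | What the article states |
|---|---|
| Who is covered? | Anyone who withdraws or is removed from the study, whatever the cause |
| What stops? | All research activity, at once |
| What is kept? | Final clinical, anthropometric and laboratory examinations, if the person is willing |
| When is that examination? | Not stated |
| Are week-4, 3-month and 6-month weights kept for a leaver? | Not stated |
| Is leaving the intervention separated from withdrawing consent to follow-up? | No |
| What analysis is promised? | Intention-to-treat and per-protocol |

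Read literally, the first sentence leaves no research activity in which the examination of the second could take place. Read together, some examination is meant, but a week-4 weight is not assured.

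**2. Room for losses.** Inputs: at least 10 per group and a 40% addition (Sample size); two blocks of six and four blocks of four (Randomization).

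- Needed: 2 × 10 = 20.
- Enrolled: 20 × 1.40 = 28. The blocks agree: 2 × 6 + 4 × 4 = 28.
- Headroom: 28 − 20 = 8, and 8 / 28 = 28.6%.

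This is an enrolment allowance, not a forecast of loss.

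**3. Why the size of any bias cannot be derived.** The following is an illustration only. Assume that completers in both arms lose the 3% target. Assume also that 5 of 14 active and 3 of 14 sham participants leave at week 2, having lost half of it (1.5%). At an assumed 85 kg, 3% is 2.55 kg and half is 1.275 kg. Differences are mean loss in active minus sham.

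- Completers only: 2.55 − 2.55 = 0.
- Exit weight treated as the week-4 value: (9 × 2.55 + 5 × 1.275) / 14 = 2.09 kg against (11 × 2.55 + 3 × 1.275) / 14 = 2.28 kg, a difference of −0.18 kg.

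The true week-4 difference depends on what happened to the leavers afterwards:

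| Leavers' week-4 loss | True difference | Error, completers only | Error, exit weight as week 4 |
|---|---|---|---|
| 2.55 kg (as completers) | 0 | 0 | −0.18 kg |
| 0 kg | 9/14 × 2.55 − 11/14 × 2.55 = 1.64 − 2.00 = −0.36 kg | +0.36 kg | +0.18 kg |

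In the second row the true difference is the gap in leaving proportions times the target loss: (5 − 3)/14 × 3% = 0.43% of body weight. With the same eight leavers split 4 and 4 it would be zero. With all eight in one arm it would be 8/14 × 3% = 1.71%, or 1.46 kg at 85 kg. Size and sign therefore turn on the split between arms and on the leavers' week-4 weights, and the rule does not secure the latter.

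**4. What the weekly weights add.** They exist up to exit, on the same scale, and can enter the GEE at their own times. They are taken after a 3-hour fast, whereas the Anthropometric assessment section asks for a morning measurement, fasting and without exercise in the previous 24 hours. They are useful but not the same measurement, and under the rule they end when the person leaves.

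**The case against.** The best defence is that the protocol does not abandon leavers. The sentence after the rule offers them a final examination that includes anthropometry, and hence a weight. Its content resembles the assessment that the Study protocol section repeats at the end of treatment, so it may mean attendance at week 4. Those who refuse cannot be compelled under any protocol. The trigger is leaving the study, and stopping research activity when someone withdraws is ordinary. Finally, this is a condensed article, and detailed retention procedures may sit in the full protocol.

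Much of this stands, and it rules out several stronger readings:

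- **That intention-to-treat will lack a week-4 weight for everyone who leaves.** Willing leavers are examined, at a time that is not given.
- **That stopping stimulation or the diet means removal.** The article does not say so. Missed sessions are made up at the weekend, and non-adherent participants are classified as such with no mention of removal.
- **That an exit weight will replace the week-4 value.** No such substitution is stated; the illustration above only shows what it would do.
- **That the result will be a completers' result.** Weekly weights up to exit can contribute to a model of group by time.
- **That GEE is unbiased only under missingness completely at random.** This is too absolute: missingness that depends only on modelled covariates is also acceptable, and a well-specified working correlation can reduce bias. These choices may be in an analysis plan that is not shown.
- **That per-protocol has equal rank.** Both sets are merely listed; their ranking is commonly left to the analysis plan.

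The defence does not remove the conflict between the two sentences, the missing time point, or the inclusion of people removed by the team who would still attend. The article states the rule outright, so this is not simply detail left to a fuller document.

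**Conclusion.** The concern holds in a limited form. The article states a rule that ends research activity for all leavers, follows it with an examination at an unfixed time, and then promises intention-to-treat. Week-4, 3-month and 6-month weights are consequently not secured for randomised participants who leave but would still be weighed. It does not follow that those weights will all be missing.

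The plan's own figures leave room for 8 of 28 participants (28.6%) to go before the target of 20 is missed, so the matter is not trivial. Whether bias results depends on leaving being related to weight change, which is plausible but not shown. Its size cannot be derived from the document; the kilogram figures above rest on assumed inputs and point in opposite directions under opposite assumptions. The wording should be changed, because weights that were never taken cannot be recovered at analysis.

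**What to change.** Reconcile the sentences in Intervention procedures so that they say three things:

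1. A randomised participant who stops, or is removed from, the intervention is still asked to attend the scheduled weight assessments at week 4, 3 months and 6 months, unless that person withdraws consent to data collection.
2. The final examination has a stated time.
3. Any weight taken earlier, at exit, is recorded with its date and analysed at its actual time, not as the week-4 value.

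This concerns data collection only and changes no rule on treatment. The visits are already scheduled and the Trial status section describes the trial as ongoing, so a small amendment would still help participants not yet past those visits. The cost is some contact effort for people who have stopped.

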##### Hypocaloric diet

The energy deficit will be calculated for each participant individually using the online Body Weight Planner program, which is a validated dynamic simulation model of human metabolism recommended by the National Institute of Diabetes and Digestive and Kidney Diseases for prescribing weight loss diets [52]. Using the information on age, sex, height, weight, and physical activity level, the number of kilocalories per day needed to alter a specific amount of weight in a certain number of days can be determined.

The prescribed hypocaloric diets will conform to American Diabetes Association specifications for overweight or obese patients with type 2 diabetes or prediabetes. The planned macronutrient profile will be 45–50% of total energy intake as carbohydrates, with emphasis on a low glycemic index; 15–25% as protein; ≤ 30% from fat, with unsaturated fats being the main source (saturated fat limited to < 7%); and ≥ 20 g/d or 14 g/1000 kcal/d as fiber [53].

Compliance with this diet and changes in food consumption from baseline will be assessed using the 3-day WDR technique at three different times: at baseline, as described in the “Eating behavior assessment” section above, at the end of the first 2 weeks, and again during the last 2 weeks of the study, totaling nine WDRs. The diet composition, obtained from the prescribed diet and from the 3-day WDRs, will be analyzed (U.S. Department of Agriculture table [54]) in NutriBase 17 Pro Edition software (version 17.2; CyberSoft, Inc., Phoenix, AZ, USA). The mean values for energy and nutrients consumed during the 3-day WDR will be calculated. Patients will be classified as adherent or nonadherent according to whether or not they will reach their calculated energy goals and diet recommendations.

##### Transcranial direct current stimulation

The tDCS technique consists of applying a weak constant electrical current (typically 1.0 to 2.0 mA) through two surface electrodes placed on the scalp to modulate brain activity in a polarity-dependent fashion; that is, anodal stimulation typically increases spontaneous neuronal excitation (depolarization), whereas cathodal stimulation has the opposite effect (hyperpolarization).

A battery-driven direct current stimulator called the Chattanooga Ionto™ Dual Channel Electrophoresis System (DJO Global, Guildford, UK) will be used in this protocol. Direct current (2 mA) will be delivered over the right DLPFC through a pair of 35-mm^2^, 0.9% saline-soaked surface sponge electrodes placed according to the 10–20 International System of Electrode Placement (EEG 10/20). The right DLPFC position will be found according to Beam et al.’s methods [55]. This system accounts for variability in subject skull size by using certain percentages of the circumference and distances between four basic anatomic landmarks (right and left tragus, nasion, and inion). We will use Beam F3 Locator software, which was developed to more accurately determine where the electrodes should be placed on the skull [56].

The participants will be randomized to receive either active or sham tDCS treatment. While following the hypocaloric diet, they will undergo 20-minute daily tDCS sessions each weekday (including holidays) for 4 weeks (20 total sessions). If a scheduled tDCS session will be missed for any reason, it will be made up the following weekend. The participants will be instructed not to consume food 3 hours before each stimulation session. Each session will be conducted at the same time of day for each participant, and only trained technicians will perform tDCS.

For active tDCS, the electrodes will be placed with the anode electrode over the right DLPFC (F4) and the cathode electrode over the left DLPFC (F3), using the technique described above. The current will be ramped up for 15 seconds until it reaches 2 mA, and the participants will then be stimulated for 20 minutes. The current will then be ramped down for another 15 seconds and will be turned off. For sham tDCS, the electrodes will be placed identically to those in the active group, but the current will be ramped up to 2 mA and then back down in the first and last 30 seconds of the 20-minute session. As a result, the participants will feel the initial itching sensation associated with turning on the device but will receive no stimulation for 19 minutes of the session.

During the sessions, the subjects will also be exposed to a series of high-calorie food images previously demonstrated to stimulate the appetite. Three different sets of 200 pictures of high-calorie and highly palatable foods, such as sweets, high-fat foods, and traditional meals, will be shown to participants as a video presentation during the 20-minute sessions, with a 6-second interval between pictures. The participants will be asked to pay attention to these images and turn off phones, pagers, or other devices that might distract their attention.

In addition, the participants’ subjective feelings of desire to eat, mood, and attention will be assessed immediately before and after the first, tenth, and twentieth tDCS sessions with a VAS, as described in the “Anthropometric assessment” section above. The aim is to verify the presence of acute effects on the desire to eat after visual stimuli associated with tDCS.

Because effects such as headache, scalp burning, tingling, and dizziness have previously been associated with tDCS, the participants will be asked about adverse effects twice each week at the end of a stimulation session, as well as whether they had experienced any such effects after the previous session.

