#### Data analysis

To compare the participants’ baseline characteristics, Student’s *t* test and the chi-square test will be used as appropriate. The results will be expressed as mean ± SD, mean (95% CIs), or the number of patients with the characteristic (percent). The Shapiro-Wilk test will be used to verify data normality; variables with non-Gaussian distribution, such as insulin and the HOMA index, will be logarithmically transformed before analysis when necessary. The aRMR will be performed using logarithmically transformed data, as recommended by Kaiyala and Schwartz [40].

The effects of tDCS between groups over time will be analyzed using the generalized estimating equation (GEE), including tDCS group, time, and the group- and subgroup-by-time interaction as predictors. All GEE models will be followed by a Bonferroni post hoc analysis and the least significant difference test to identify significant differences detected by the GEE. Gamma distribution with log link function will be used for variables with non-Gaussian distribution. After treatment of the first ten participants, an interim security analysis was planned, and the trial may be stopped prematurely because of safety concerns, such as severe psychiatric and neurologic reactions. The outcomes will be presented as *p* values for the included factors and estimated marginal means, with corresponding 95% CIs for each tDCS group at each time point. A *p* value < 0.05 will be considered statistically significant. IBM SPSS Statistics version 19.0 statistical software (IBM, Armonk, NY, USA) will be used for the analyses.

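### Adverse effects are asked about twice a week although stimulation is given five times a week, so at most 16 of 20 sessions are covered in any way and at most 8 of 20 for delayed effects

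*Protocol article*

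**What the plan says.** The Methods/design part of the abstract sets the course as "20 sessions; 5 consecutive weekdays/wk, 2 mA, 20 minutes". The section Transcranial direct current stimulation repeats the total of 20 and adds: "If a scheduled tDCS session will be missed for any reason, it will be made up the following weekend". A missed weekday therefore moves a session but does not remove it.

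The same section fixes the safety questioning. Its reason is given as "Because effects such as headache, scalp burning, tingling, and dizziness have previously been associated with tDCS". The rule is that "the participants will be asked about adverse effects twice each week at the end of a stimulation session". Each enquiry also looks back by one session, in these words: "as well as whether they had experienced any such effects after the previous session".

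The article describes no other scheduled enquiry about adverse effects during treatment. The visual analogue scales at sessions 1, 10 and 20 concern desire to eat, mood and attention. The weekly dietitian visit concerns the diet.

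The section Data analysis plans one safety look: "After treatment of the first ten participants, an interim security analysis was planned, and the trial may be stopped prematurely because of safety concerns". The Discussion calls the technique safe and well tolerated. It also says that a 20-session course has not been reported for this use, though courses of 5 to 30 daily sessions are common in other conditions.

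**The concern.** The questioning is less frequent than the exposure, and its only explicit look-back is one session. Two enquiries a week cannot cover five sessions, whichever days are chosen. Delayed effects are hit hardest, because each enquiry reaches only the one session before it. For session 20 there is no later session at which to ask.

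The effects that prompt the questioning (headache, scalp burning, tingling, dizziness) are mostly mild and short-lived, and such effects may go unmentioned unless someone asks. If the trial is later used to describe how well a 20-session course is tolerated, the counts will be incomplete by an unknown amount. The contact needed for complete capture already exists, because a trained technician sees each participant at every session.

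**Working it through.** **Inputs from the protocol article**
- 5 sessions a week for 4 weeks (abstract; Transcranial direct current stimulation).
- 2 enquiries a week, each at the end of a session (same section).
- Each enquiry covers the session just ended and, for effects afterwards, the one before it (same section, plain reading).

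**The plan's own figure.** 5 × 4 = 20 sessions, which matches the stated total. The article states no coverage figure, so there is none to reproduce.

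**Upper bounds**
- Enquiries per participant: 2 × 4 = 8.
- Sessions asked about at their own end: 8 of 20 (40%).
- Sessions asked about for delayed effects: at most 8 of 20 (40%). If session 1 is an enquiry session it has no predecessor, and the figure is 7 of 20 (35%).
- Sessions covered in any way: at most 8 + 8 = 16 of 20 (80%), so at least 4 are not covered.

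**Dependence on the days chosen** (same two days every week, sessions numbered 1 to 5 within the week)

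| Enquiry sessions | Covered in any way | Delayed effects asked | Both kinds asked |
|---|---|---|---|
| 2 and 4, 2 and 5, or 3 and 5 | 16 | 8 | 0 |
| 1 and 3, or 1 and 4 | 15 | 7 | 0 |
| 2 and 3, 3 and 4, or 4 and 5 | 12 | 8 | 4 |
| 1 and 5 | 12 | 7 | 3 |
| 1 and 2 | 11 | 7 | 4 |

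If the days may differ from week to week, there are 10⁴ placements. Across all of them coverage runs from 10 to 16 of 20. Wherever it reaches 16, no session is asked about for both immediate and delayed effects. Weekend make-up sessions leave the 16-of-20 and 8-of-20 ceilings unchanged, because the totals stay at 20 sessions and two enquiries a week.

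**Precision.** If sessions were independent, the standard error of a per-session rate from 8 rather than 20 sessions would be larger by √(20/8) = 1.58. If a susceptible participant reacted at every session, 8 enquiries would lose nothing and the factor would be 1. The truth lies somewhere between.

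**Illustration at the ten-participant look.** With 1:1 allocation about five of the ten are on active stimulation, giving 5 × 20 = 100 active sessions, of which at most 5 × 8 = 40 are asked about for delayed effects. Assume a delayed effect in 1% of active sessions, independent sessions and no spontaneous reporting; none of these comes from the article. The chance of recording at least one is 1 − 0.99⁴⁰ = 33%, against 1 − 0.99¹⁰⁰ = 63% if every session were asked about. Clustering within participants or spontaneous reports would shrink this difference.

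**Coverage after the change.** Asking both questions at every session covers 20 of 20 for immediate effects and 19 of 20 for delayed effects. One question at the end-of-treatment assessment supplies the last.

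**The case against.** The schedule is stated plainly and nothing in the article contradicts it. The article never promises capture at every session and lists no adverse-event rate among its outcomes. A condensed article also commonly leaves spontaneous and serious event reporting to the full protocol. All this stands: the point is a cheap improvement to a stated rule, not an error or an omission.

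The general question is not expressly limited to the session just ended and could be meant to cover the time since the last enquiry. That cannot be excluded. The narrower reading is more natural, because a separate clause about the previous session would be superfluous if the general question already reached back further.

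Three stronger conclusions are tempting, and the document does not support them.

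- A reader might infer that the comparison between arms is biased or that event rates are understated. Both arms follow the same schedule, and a rate per queried session is not lowered by querying fewer sessions. What suffers is the completeness of absolute counts and their precision.
- A reader might infer that the safety look would miss what it exists to find. Data analysis says that "the trial may be stopped prematurely because of safety concerns, such as severe psychiatric and neurologic reactions". Reactions of that kind, in someone seen every weekday, would probably come to light unasked, and the article does not say that this questioning is the look's main input.
- A reader might infer that session 20 goes entirely unobserved. Under Study protocol the baseline assessment is repeated after treatment, and under Clinical interview it includes a medical history and a physical examination. That partly covers session 20, though no adverse-effect question is specified there.

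**Conclusion.** The point holds as a modest weakness in safety data collection. On the plain reading at least 4 of 20 sessions per participant fall outside the scheduled questioning, and at least 12 of 20 are never asked about for delayed effects. These are best-case figures for the plan; an unlucky choice of days leaves up to 10 of 20 uncovered. They rest on each enquiry reaching back exactly one session and take no account of spontaneous reports.

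The consequence is confined to mild, transient or delayed effects: incomplete counts, and a standard error between 1 and about 1.6 times that of full questioning, depending on how strongly effects cluster within participants. This matters more because the trial is small (the randomization blocks sum to 2 × 6 + 4 × 4 = 28 participants) and the course length is new for this use. The efficacy outcomes are unaffected.

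**What to change.** At every session, in both arms and with identical wording, ask one short checklist in two parts: before stimulation, any effects since the last session; at the end, any effects during this session. Ask the first part once more at the existing end-of-treatment assessment, so that session 20 is covered. Tabulate by arm, per participant and per queried session, with separate denominators for immediate and delayed effects. Make these data available to the planned safety look.

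The article reports the trial as ongoing. If the change is adopted part-way, apply it to both arms from the same date and label data collected before then as partly queried. If the ten-participant look has already taken place, the gain is in the final safety tables only.

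The cost is a minute or two at visits that already happen, with no new visit, staff or procedure. The downside is that more minor events will be recorded in both arms. Only data collection changes.
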